## Abstract

**Background:**

Anhedonia is generally defined as the inability to feel pleasure in response to experiences that are usually enjoyable. Anhedonia is one of the two core symptoms of depression and is a major public health concern. Anhedonia has proven particularly difficult to counteract and predicts poor treatment response generally. It has often been hypothesized that anhedonia can be deterred by a healthy lifestyle. However, it is quite unlikely that a one-size-fits-all approach will be effective for everyone. In this study the effects of personalized lifestyle advice based on observed individual patterns of lifestyle behaviors and experienced pleasure will be examined. Further, we will explore whether a tandem skydive following the personalized lifestyle advice positively influences anhedonic young adults’ abilities to carry out the recommended lifestyle changes, and whether this ultimately improves their self-reported pleasure.

**Methods:**

Our study design is an exploratory intervention study, preceded by a cross-sectional survey as a screening instrument. For the survey, 2000 young adults (18–24 years old) will be selected from the general population. Based on survey outcomes, 72 individuals (36 males and 36 females) with persistent anhedonia (i.e., more than two months) and 60 individuals (30 males and 30 females) without anhedonia (non-anhedonic control group) will be selected for the intervention study. The non-anhedonic control group will fill out momentary assessments of pleasure and lifestyle behaviors three times a day, for one month. The anhedonic individuals will fill out momentary assessments for three consecutive months. After the first month, the anhedonic individuals will be randomly assigned to (1) no intervention, (2) lifestyle advice only, (3) lifestyle advice plus tandem skydive. The personalized lifestyle advice is based on patterns observed in the first month.

**Discussion:**

The present study is the first to examine the effects of a personalized lifestyle advice and tandem skydive on pleasure in anhedonic young adults. Results of the present study may improve treatment for anhedonia, if the interventions are found to be effective.

**Trial registration:**

Dutch Trial Register, NTR5498, registered September 22, 2015 (retrospectively registered).

**Electronic supplementary material:**

The online version of this article (doi:10.1186/s12888-016-0880-z) contains supplementary material, which is available to authorized users.

## Background

Anhedonia is generally defined as the inability to feel pleasure in response to experiences that are usually enjoyable [1]. Anhedonia is one of the two core symptoms of depression and common among young people: almost 20 % of adolescents from the general population have experienced episodes characterized by marked loss of interest in things they usually enjoy at least once in their lives [2]. Anhedonia is of major public health concern and is a dreadful experience for those who suffer from it, causing a sense of disengagement from the surrounding world and increased risk of suicide [3]. Treatment of anhedonia has received growing attention last years. It has proven particularly difficult to counteract [1] and predicts poor treatment response generally [4]. Deep brain stimulation to reward circuitry has been shown to alleviate anhedonia in treatment-resistant depressed patients [5, 6], but is too costly and invasive for large-scale application, and may lead to memory loss. Hence, we need innovative approaches to help the field forward. The challenge is to find non-invasive, non-pharmacological ways to restore a dysregulated reward system.

It is well-established that a substantial proportion of the population suffers from loss of pleasure, but less well established how exactly this loss is expressed in various aspects of life. Anhedonia is a multi-faced concept in many respects [7], and little is known about the interrelations and associated factors of these dimensions of anhedonia. To start with, individuals can experience losses in one or more different domains [8], such as food, sexual, social, and aesthetic pleasures. Heterogeneity within these domains likely arises due to the presence of different dimensions of anhedonia: consummatory versus anticipatory versus motivational anhedonia [1, 9–11]. Consummatory anhedonia concerns the pleasure experienced while experiencing a stimulus; anticipatory anhedonia involves the pleasure experienced in anticipation of a stimulus; and motivational anhedonia is about approach motivation, that is, how much effort one is willing to invest to reach a specific anticipated pleasure. So far, very little research has focused on exploring the interrelations between these different types of anhedonia.

The proposed study, which is imbedded in the project ‘*No fun no glory: a biopsychosocial investigation of how adolescents lose the ability to experience pleasure and may gain it back again’* (NWO Vici 016.001/002, granted to Prof. dr. [name]), will use state-of-the-art biopsychosocial methods to understand better what causes and sustains anhedonia, and explore the potential of a non-invasive ‘shock’ to reboot a dysregulated reward system. It has often been hypothesized that anhedonia can be deterred by a healthy lifestyle and engagement in stimulating social and physical events [12–14]. However, it is quite unlikely that a one-size-fits-all approach will be effective for everyone. As an alternative to interventions designed for typical or averaged responses, personalized medicine takes into account individual responses to potential change agents [15, 16]. Several researchers have pointed towards using ambulatory assessment as a possible tool for providing insight in daily life patterns of mood [17, 18]. Previous research in depressed patients has shown that providing feedback based on personalized patterns of positive affect is effective in decreasing depressive symptoms [19]. In our intervention study we will examine the effects of tailor-made lifestyle advice, as a non-pharmacological means to restore the pleasure of everyday activities and accomplishments, based on observed individual temporal patterns of lifestyle behaviors and experienced pleasure. Regardless of whether the advice is tailor-made or not, lifestyle changes are particularly hard to achieve or maintain for anhedonic persons, because their symptoms bereave them from the drive to pursue rewarding activities. As anhedonic persons are stuck in a spiral that is hard to break out of, mild interventions may not be effective and an intense experience may be needed to kick-start the reward system. This provocative thought will be explored in our intervention study as well, by examining whether exposure to a tandem skydive experience can help to get the reward system going again and so foster the recommended lifestyle changes that can restore the ability to experience pleasure. Thrill-experiences provide strong boosts of dopamine, and skydiving is considered an acceptable and valid human model for eliciting such responses [20, 21].

The first reason to suspect that tandem skydiving might have an effect on anhedonia is that it provokes strong emotions. Even though people rationally know that a tandem skydive is quite safe, the perception of falling down from a great height is so alarming to the brain that it elicits a fight-flight response in almost all individuals [22]. The immediate physiological response is for example reflected in increases in heart rate, blood pressure, catecholamines and cortisol levels, all of which usually return to pre-stress values not too long after the thrill experience has ended [21]. Psychologically, most people experience intense fear during the experience [22], followed by euphoria afterwards [23]. This affective contrast may be explained by Solomon’s Opponent Process Theory of Acquired Motivation, which states that humans innately contrast extreme experiences, and that removal of one emotion (in this case fear) produces the opposite response (euphoria). Another explanation for the often-reported positive feelings after a thrill experience is that conquering one’s fear boosts self-confidence and self-image [24]. These positive emotions seem an excellent start to implement life style changes that promote more persistent positive feelings.

A second reason for hypothesizing beneficial effects of tandem skydiving is that extreme experiences may shake up and reset the way how individuals respond to their environment. It is hard to predict precisely how tandem skydiving will act upon the drive to engage in pleasurable activities, because many systems are triggered in parallel. However, this is not unlike another intervention which has proven highly effective to improve mood and anhedonia in particular circumstances: electroconvulsive therapy (ECT) [25, 26]. ECT affects a wide range of neurobiological components, and numerous mechanisms have been proposed which all seem plausible [27–30]. Despite obvious differences between ECT and a tandem skydive experience, both shock experiences may set the stage for change.

In humans, not much is known about biological pathways through which experiences like tandem skydiving may induce changes in behavior and emotions. We want to address potentially relevant biological pathways in this study. By repeatedly measuring the blood markers dopamine [31, 32], serotonin [31], oxytocin [33], adrenalin, noradrenalin [34] and BDNF [27, 28, 35, 36], we will investigate specific mechanisms through which a tandem skydive accompanied by personalized lifestyle advice may help in regaining pleasure. In addition, we will assess the biomarkers BDNF and alpha-amylase around the skydive, to examine acute mechanisms of change [27, 28, 37]. Finally, previous research has shown that genes involved in the dopaminergic system, notably COMT and DAT [38, 39], as well as the BDNF gene [40] are related to reward processing, and that individuals with certain genetic variants in the DRD4 [41] and the SCL6A4 [42] gene are more susceptible for treatment. Further, animal research provided evidence that electroconvulsive therapy affects the expression of the BDNF gene, through epigenetic changes [43]. Hence, (epi)genetic factors may help explain why the intervention is or is not effective in reducing anhedonia.

In sum, the primary objectives of the current three-arm, parallel group, superiority randomized controlled trial are to examine (1) the effects of tailor-made lifestyle advices, as a non-pharmocological means to restore the pleasure in everyday activities and accomplishments and (2) whether exposure to tandem skydiving, an experience known to activate the dopamine system and to elicit strong emotions, can help to reboot the reward system and hence foster the recommended lifestyle changes. The effects of the interventions will primarily be examined with regard to experienced pleasure, but changes in blood and saliva levels of potential biomarkers are also taken into account. The secondary objectives of the current study are to (1) elucidate the various faces of pleasure loss (i.e., the different domains and dimensions) and investigate how often and in which combinations they occur among young adults, and (2) investigate relations between the various domains and dimensions of anhedonia and other factors, among which mental health problems, lifestyle behaviors, personality, self-efficacy, self-perceived social rank, and emotion recognition skills.

## Methods

### Participants

For the screening survey, 2000 young adults (18–24 years old) will be recruited from the general population. Inclusion criteria for the survey are age between 18–24 years and sufficient knowledge of the Dutch language. Inclusion criteria for the anhedonia group are (a) persistent pleasure loss and (b) willingness to perform a skydive. For the non-anhedonic control group, the inclusion criteria are (a) no loss of pleasure and (b) willingness to perform a skydive. Exclusion criteria are inability to keep an electronic diary three times a day; current professional treatment for psychiatric problems; current use of psychotropic medication; epilepsy; pregnancy; conditions that make it impossible to be attached to the tandem master (e.g., loose prostheses); height of more than 2 m; weight of more than 95 kg; inability to raise one’s legs 90° (needed for safe landing after tandem skydive); significant visual or hearing impairments; experience with skydiving, bungee jumping, base jumping, or skyjumping; cardiovascular complaints/problems. All criteria were included as questions in the screening survey.

We will use three questions from the Domains and Dimensions of Pleasure Scale ​(DDOPS; [name], [name], [name], [name], [name], & [name]: Domains and Dimensions of Pleasure Scale (DDOPS): a novel questionnaire to assess anhedonia, submitted) to measure persistent loss of pleasure. These questions assess the level of pleasure experienced during the past two weeks, whether this level represents a loss compared to what is considered normal to that person, and the duration of the loss. Participants who report low pleasure levels (score below the 25th percentile), a loss compared to normally experienced pleasure levels, and a minimum duration of the loss of 2 months are eligible for inclusion. We aim to complete the data collection in at least 60 anhedonic persons (20 in each condition). Because we expect some dropout during the data collection, we decided to select 24 individuals for each condition (72 in total). The non-anhedonic control group will consist of 60 individuals.

We will use stepwise inclusion for both anhedonic and non-anhedonic control participants. In the anhedonic group, we will include all participants that fulfil our criteria and are willing to participate in the study. Whenever a person is included in the anhedonic group, we will select a participant for the non-anhedonic control group, matched on sex, age, and educational level. When several control participants fulfil the criteria for matching, we will use random selection.

### Procedure

The current study will take place at the University Medical Center Groningen, the Netherlands, and uses a two-phased design. In the first phase, a survey will be administered among 2000 young adults (aged 18–24), who will be selected from secondary and higher vocational education schools in the Northern municipalities of the Netherlands, and from the University of Groningen. Participants of the survey will receive 10 Euro gift card and additionally a lottery will be held among all participants. The survey will contain, among other items, questions regarding the severity and duration of anhedonia, which will be used to select participants for the second phase of the study, i.e. the intervention part.

Individuals who are eligible for the intervention study and give permission to be contacted for further research will receive a detailed information letter and consent form by email, after which they will have one week to decide whether they want to participate. The information letter includes information about the study procedures, possible risks, insurance regulations and the possibility to stop the study at any point. Subjects who decide to participate should return a signed consent form. On the consent form, participants can indicate whether or not they give consent for storage of their body specimens for 15 years and whether or not they agree to be approached for further research in the future. Subsequently, the participants will receive an invitation for an introductory meeting during which participants’ age (checked in ID) and other exclusion criteria are discussed and checked. In addition, appointments are made and the first monthly measurements are taken.

The intervention study consists of one pre-intervention observation month, followed by two (post-) intervention months (see Fig. 1 for a flow-chart of the intervention study). During these months, a replicated single-subject multivariate time series design will be used, in which the participants will record pleasure and possibly associated factors three times a day [44, 45], using a web-based application specifically designed for this purpose (www.roqua.nl), on their own smartphones. Time series involve a detailed collection of multiple observations within subjects [46], which allows to closely delineate processes of change over time and the temporal order of effects. The many data points and small time lags offer the opportunity to assess whether changes in one variable precede, follow, or are concurrent with changes in another, and to model potential feedback influences and cyclic patterns. As a result, inferences about the timing and direction of effects can be made more validly than in most other research designs [16, 47]. Another advantage of the small intervals between the measurements is that they reduce recall bias. Individual differences are easier to detect, as the primary analyses are done at the individual instead of the group level [16], and the design offers a powerful tool to investigate the effects of interventions [48]. Finally, the data collection takes place within participants’ natural environment, making generalization to real life more plausible [49].

**Fig. 1 Fig1:**
[figure not shown]
Flowchart of the study design

After the pre-intervention observation month, the anhedonic participants will be randomly assigned (stratified on gender) to: (1) no intervention; (2) personalized lifestyle advice, based on association patterns observed in the first month; or (3) personalized lifestyle advice followed by a tandem skydive. After the second month, at the start of the third month, all participants are free to choose whatever they prefer, regardless of the intervention received after the first month: no intervention, lifestyle advice, or lifestyle advice and a tandem skydive. This last month is added to provide a more realistic impression of the feasibility and appeal of the interventions.

Before and after each observation/intervention month as well as after 6 months and one year (in total 6 times), the participants in the anhedonic groups will fill out an online questionnaire. We will collect blood samples along with the monthly and follow-up questionnaires, i.e. six times per person in total. Before and after their first skydive, participants will be asked to donate a total of four saliva samples. Saliva will be collected by means of salivettes, on which the participant has to chew. A member of the research team will provide the salivettes to the participants and provide instructions on how to use them. The salivettes will be collected by the same research member and transported to the UMCG lab.

The anhedonic intervention groups receive 75 Euro after the observation month; another 125 Euro after the first intervention month; and 200 Euro after the second intervention month. They will receive these incentives only if they reach the required compliance rate of 80% within the required time frame, if they fill out all monthly assessments and provide the required blood samples. For the two follow-up measurements they will receive 50 Euro per measurement, once assessments are filled out and blood samples are provided. This means that anhedonic participants will receive up to 500 Euro in total.

The control group of 60 non-anhedonic individuals will participate in the pre-intervention observation month only. Comparisons between this non-anhedonic control group and the intervention groups will enable us to judge whether specific daily life patterns are related to anhedonia and provide us with benchmarks with respect to the distribution and frequency of activities and associated pleasure. The non-anhedonic control group receives 75 Euro after having completed the monthly questionnaire twice and one month of momentary assessments. This fee will be conditional on the required compliance rate of 80% within the required time frame.

In order to promote retention, we will ask our participants to report any issues hampering continued participation, for example inability to fill out the diaries due to technical or practical issues (e.g., problems with internet connection, changing work schedules). We will facilitate in solutions for these issues, for example by lending mobile phones, compensating mobile internet costs and adjusting time slots for momentary assessments.

### Ethics

The present study was approved by the Medical Ethical Committee from the University Medical Center Groningen (no. 2014/508). All data received from participants will be processed in a strictly confidential manner. All participants will randomly be assigned a unique identification number, ranging from 1 to 9999. During data collection, team members will have access to the coding of the participants assigned to them in order to contact them and monitor their momentary assessments. After data collection, only the practical coordinator (TB) and the principal investigator (AO) of this study will have access to the coding of the subjects. Other investigators only have access to the coded files that do not contain information that can be traced to a specific individual. All handling of personal data will comply with the Dutch Personal Data Protection Act (Wet Bescherming Persoonsgegevens).

Although we do not expect any adverse events to occur, giving that skydiving can be considered a relatively safe sport (i.e., data from the Royal Netherlands Aeronautical Association showed no fatalities and only 0.29-0.91 minor injuries per 1000 tandem skydives in the Netherlands), we will report any serious adverse events to the medical ethical committee, according to ethical guidelines. Further, participants’ data will be monitored and if a participant’s complaints or symptoms suggest that psychiatric treatment might be indicated, we will discuss these findings with a psychiatrist in the University Center for Psychiatry, and – if the psychiatrist confirms our observation - offer that participant a consult with that psychiatrist. The study’s sponsor has an insurance to cover damage to research subjects. Further, an additional insurance covers any potential damage related to the tandem skydive.

The present study protocol was prepared in accordance with SPIRIT guidelines. The SPIRIT checklist can be found in Additional file 1.

### Randomization

Stratified by gender by means of a block randomisation procedure, participants will be randomly assigned to: (1) no intervention; (2) personalized lifestyle advice; or (3) personalized lifestyle advice followed by a tandem skydive. For males and females separately, a block size with an allocation sequence of six will be used with an equal condition distribution (i.e. each condition is present twice in a block of six). A total of 12 blocks will be created by one of the team members (MM), using an online randomisation program. The allocation will be done by other team members (i.e., ER, CV, or VH) than the one who created the allocation sequence. As it will be clear to participants which intervention they will receive, intervention allocation cannot be blinded to participants nor to the research team.

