### Statistical analyses

#### Primary outcome variables

First, we will examine individual response patterns by means of (interrupted) time series analysis (ITS) to detect time trends in the amount of pleasure experienced during the study, and differences in the level and slope between pre- and post-intervention pleasure levels. Interrupted time series analysis is particularly useful to test changes in outcome rates in time periods before and after implementation of an intervention designed to change the outcome (see, for instance, [53]). The number of individuals who show a significant improvement in pleasure in the second month of the study period as compared to the first one will be compared across the three intervention groups to assess to what extent this improvement, if any, is likely to be due to spontaneous recovery or the mere daily registration of pleasure and activities, to the personalized lifestyle advice, or to the tandem skydive experience. In addition, we will explore whether changes in pleasure scores from pre- to post-intervention differ between the three intervention groups in a multilevel model. We will compare both (a) individuals who did and did not receive lifestyle advice; and, within the group who received lifestyle advice, (b) individuals who did and did not perform a skydive. We will use a multilevel model with two levels, in which Level 1 represents the momentary assessments, and Level 2 the individual level (e.g., intervention group). The main advantage of multilevel analyses is that it takes the nested structure of the data into account. By conducting multilevel analyses, we will be able to compare post-intervention mean levels of momentary pleasure between the three intervention groups, while controlling for the level of pleasure in the pre-intervention period (i.e., the observation month).

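### The reason given for leaving the research team unblinded does not cover whoever fits the individual pleasure series; improver status could be classified without arm at small cost

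*Protocol article*

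**What the plan says.** The Randomization section of the protocol article gives a reason, "As it will be clear to participants which intervention they will receive", and concludes from it that "intervention allocation cannot be blinded to participants nor to the research team". It exempts no role.

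The section Primary outcome variables makes the first primary analysis an interrupted time series for each participant, with level and slope terms. It then compares "The number of individuals who show a significant improvement in pleasure in the second month of the study period", relative to the first month, between the three arms. A multilevel comparison of the arms follows as an additional analysis.

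The Ethics section says that while data are being collected, team members hold the coding of the participants assigned to them. Afterwards only the practical coordinator and the principal investigator keep it: "Other investigators only have access to the coded files". That rule protects identity. It does not say whether the coded files carry arm.

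**The concern.** The stated reason and the stated conclusion differ in scope. Participants cannot be masked to receiving advice or a skydive, and neither can the staff who provide them. Fitting a model to a series of pleasure scores is a different task, and nothing in the Randomization section shows that it requires the arm.

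The task leaves room for judgement. A yes/no verdict on each series depends on how trend and autocorrelation are handled and on whether a change in level, in slope or in both counts as improvement. The article gives no criterion beyond significance. If such choices are made person by person with the arm in view, they can tilt the improver count, which is the quantity compared between arms.

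**Working it through.** **Number of series.** Randomization: 12 blocks × 6 = 72. Participants: 3 arms × 24 = 72. The two agree. The Participants section aims for complete data in at least 3 × 20 = 60, and the Missing data section excludes anyone below 80% compliance in the first month. So there are up to 72 individual models, with at least 60 targeted.

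**Where arm enters the first primary analysis.**

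1. Fit each person's series: needs the pleasure scores and the boundary between months 1 and 2.
2. Classify the person as improved or not, month 2 against month 1: needs the fitted model only.
3. Compare the counts between arms: needs arm.

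The contrast in step 2 is the same in every arm, so steps 1 and 2 can be finished before arm is known. This requires the break to sit at the common month boundary, because actual advice or skydive dates would reveal arm.

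**Possible size of the bias (illustration).** The documents give no figure for this. The assumptions are:

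- a person with no true change is called improved when a standard normal statistic exceeds 1.96, so one fixed specification gives 2.5%;
- an unmasked analyst keeps the most favourable of *k* specifications whose statistics have common correlation *r*.

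The false-improver rate is then P(max of *k* > 1.96). The excess per arm is 20 × (rate − 0.025).

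| k | r | False-improver rate | Ratio to 2.5% | Excess per arm of 20 |
|---|---|---|---|---|
| 1 | – | 0.025 | 1.0 | 0 |
| 2 | 0.8 | 0.039 | 1.6 | 20 × 0.014 = 0.28 |
| 2 | 0.7 | 0.042 | 1.7 | 20 × 0.017 = 0.34 |
| 3 | 0.8 | 0.049 | 2.0 | 20 × 0.024 = 0.48 |
| 3 | 0.7 | 0.055 | 2.2 | 20 × 0.030 = 0.60 |

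Simulation and numerical integration agree on these rates. As an extreme case, five uncorrelated specifications give 1 − 0.975⁵ = 0.119, an excess of 20 × 0.094 = 1.9 persons. Different specifications fitted to the same series would not be uncorrelated, so this is an upper bound for five.

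**How sensitive the comparison is.** With hypothetical counts and 20 per arm, 8 against 2 improvers gives a two-sided Fisher p of 0.065, and 9 against 2 gives 0.031. One reclassified person matters only if the result already lies at that edge.

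**The case against.** The strongest reply is that the article never says who fits the models. The sentence stands in a section on allocation, and as a description of the people running the study it is candid. Who analyses which file is commonly left to a full protocol or analysis plan, neither of which is shown. This stands to the extent that a reader might infer that those who deliver the advice also classify the improvers. The documents do not say so. The point survives because the article does not leave the matter open: it states that the research team cannot be blinded, for a reason that does not reach the analysis.

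A reader might also infer that masking would be free. That is not shown. Team members hold participants' codes and monitor their diaries (Ethics), and first-month series are modelled to write the advice (Personalized lifestyle advice). Someone who did that work may recognise a series.

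A third reply is that the article also describes the models as pre- against post-intervention, so breaks might be set at actual intervention dates. The improver count itself is defined by month, however, and the no-intervention arm has no intervention date. A common boundary is therefore consistent with the article.

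Finally, masking alone does not remove freedom of choice. A masked analyst who picks favourable specifications still inflates false improvers, but in all arms alike. This is correct, and it is why the fix pairs masking with a fixed rule.

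**Conclusion.** The point holds in a limited form. The Randomization section gives no valid reason why the individual models and improver classifications must be made with knowledge of arm, and the month-based contrast allows them to be made without it.

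The likely effect is small. The excess is 1.4 to 3.0 percentage points, or 0.3 to 0.6 of one person per arm of 20. It rests on assumed numbers and correlations of specifications and on an analyst who exercises the choice in one direction. A reader might infer that the result is already biased, or that several classifications would be overturned. Neither the documents nor these figures support that.

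The point concerns the improver count. The multilevel comparison does not use that count. Analyst masking also leaves untouched the reporting bias that can arise because pleasure is self-reported by participants who know their arm. The study is declared exploratory, and the label is a cheap improvement.

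**What to change.** Amend the Randomization sentence to say that participants and intervention staff are not blinded, but that individual models and improver classifications are made without knowledge of arm. Then state the procedure:

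1. Prepare a coded file holding only the pleasure series and the month (1 or 2), with no arm, intervention dates or free-text activities.
2. Fit every series (up to 72; at least 60 targeted) by one specification rule fixed beforehand, with the break at the common month boundary.
3. Preferably give this to a team member who neither allocated nor advised participants.
4. Lock all classifications, and only then have the holder of the code merge arm.

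The cost is one extra file-handling step on top of the coded files already foreseen. Sample size, alpha, power and data collection do not change. The downside is that masking may be imperfect where an existing team member recognises a participant's series.
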